### Primary outcomes

8.1

Data on loneliness will be collected by administering the SELSA-S and evaluated as a total and also divided in 3 subscales: romantic, social, and familiar. Higher scores indicate a higher level of loneliness, while lower scores indicate a lower level of loneliness.

### Secondary outcomes

8.2

Data on motor ability as response time and performance in the games in a VR environment will be collected during the practice of the Reaction Time, Random, and MoviLetrando games. Lower response time and higher performance (demonstrated by higher scores and fewer errors) will indicate an improvement in motor ability.

### Data analysis

8.3

Excel and SPSS version 2.1 for Windows will be used for data preparation and analysis. The significance level will be *P* ≤ 0.05.

The data will be presented as means and standard deviations and in frequency tables. Before the data analysis, the normality of all variables will be evaluated for skewness and kurtosis. To compare participants’ mood and loneliness, paired *t* tests, Kruskal–Wallis tests, Mann–Whitney *U* tests, or Pearson correlation coefficients will be used. The analysis will be blinded and will compare the 3 moments of data collection and the 2 groups (G1 and G2). To guard against the possibility of type 1 errors from making too many post hoc comparisons, we will carry out only those comparisons that have been planned based on our hypotheses.

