**Methods and Analysis::**

This study will be a prospective longitudinal study with a randomised cross-over design, with subjects aged 50 years and older, of both genders, spontaneously enrolled in computer classes for beginners. Data collection will be done in 3 moments: moment 0 (T0) – at baseline; moment 1 (T1) – after 8 typical computer classes; and moment 2 (T2) – after 8 computer classes which include 15 minutes for practicing games in VR environment. A characterization questionnaire, the short version of the Short Social and Emotional Loneliness Scale for Adults (SELSA-S) and 3 games with VR (Random, MoviLetrando, and Reaction Time) will be used. For the intervention phase 4 other games will be used: Coincident Timing, Motor Skill Analyser, Labyrinth, and Fitts. The statistical analysis will compare the evolution in loneliness perception, performance, and reaction time during the practice of the games between the 3 moments of data collection. Performance and reaction time during the practice of the games will also be correlated to the loneliness perception.

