Research on computer classes to elderly, shows that, given appropriate structures of teaching and learning specific to older adults, elderly individuals can learn these skills even though aging can make it more challenging.^[6]^ The psychosocial impact on older adults who learned how to use the Internet was positive, showing a trend toward decreased loneliness and depression.^[8]^ One possibility for helping older adults learn effective use of ICT is via virtual reality (VR), which in general is a useful tool to study, evaluate, and rehabilitate cognitive processes and functional activities.^[9]^

VR allows the performance of new tasks and might stimulate the practice of communicative and cognitive skills, benefiting functional improvement and initiating the contact of older adults with the modern technology. Still, game software can stimulate and, also, store responses, differently from other preconized methods.^[10]^ Virtual games and virtual environments can be used as physical, cognitive, or psychological interventions to enable function and fun for different people.^[11]^ By using VR, it is possible to promote flexibility and control in task administration, increasing the chance of transferring an acquired ability in an efficient and safe way.^[12]^

Regarding VR utilization for older adults, there are studies on postural control,^[13]^ balance, fall prevention, physical activity incentives, and functional performance.^[14]^ The positive effects of using a VR game included improving physical function, decreasing depression, and increasing cognition and quality of life in older adults. Improved socialization and motivation to exercise were also reported.^[15]^ Most of the studies that assess older adults in virtual tasks were done with older adults with acquired physical and cognitive diseases, and the healthy older adults were only part of the control group.^[16]^ However, the use of VR as a means of facilitating the use of computers and reducing loneliness of healthy older adults is scarce.

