### Intervention

2.5

There are 6 groups of computer classes for beginners offered by CRI, with a maximum of 10 students each. The classes last 2 hours, twice a week and include basic computer operations, the use of Word programs and introduction to the Internet.

For the intervention, the 6 classes of computer lessons for beginners will be randomly assigned into 2 groups, group 1 (G1) and group 2 (G2), with the same number of classes for each group.

The intervention will be divided into 2 phases, as shown in Fig. 1. In phase 1, G1 will have 8 conventional computer classes, while G2 will have 8 computer classes which will include 15 minutes of practicing games in a VR environment, using a physical interface (keyboard or mouse). In phase 2, intervention will be crossed between the groups. Therefore, G2 will have 8 conventional computer classes, while G1 will have 8 computer classes which will include 15 minutes of computer game practice. The games used for intervention (Labyrinth, Fitts, Motor Skill Analyzer [MOSKA], and Timing Coincident) will be described in the section Games for training.

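### Section 8.3 ties no test to the VR-versus-conventional contrast on loneliness, so a before/after paired t test that mixes course and VR effects could be reported as the VR effect

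*Protocol article*

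**What the plan says.** The main objective (Section 1) is comparative: the effect on loneliness of VR games within computer classes, set against conventional classes. Section 2.5 supplies the means. Six classes are randomised, three to each group. In each of two phases one group has VR classes while the other has conventional ones, and the groups then swap. Loneliness is measured by "administering the SELSA-S and evaluated as a total and also divided in 3 subscales: romantic, social, and familiar".

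The list of tests in Section 8.3 opens with "To compare participants’ mood and loneliness, paired *t* tests"; in full, it states that "paired *t* tests, Kruskal–Wallis tests, Mann–Whitney *U* tests, or Pearson correlation coefficients will be used". It adds that the blinded analysis "will compare the 3 moments of data collection and the 2 groups (G1 and G2") and that only comparisons planned from the hypotheses will be run. "The significance level will be *P* ≤ 0.05". It does not say which test serves which comparison.

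The Abstract describes the analysis by time alone: "The statistical analysis will compare the evolution in loneliness perception, performance, and reaction time during the practice of the games between the 3 moments". The Abstract and the opening of Section 8 also describe one order for everyone, conventional classes first and games second, whereas Sections 2.5 and 2.6 describe the cross-over.

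On the course itself, the Introduction cites earlier work: "The psychosocial impact on older adults who learned how to use the Internet was positive, showing a trend toward decreased loneliness and depression". Section 2.5 says the classes "include basic computer operations, the use of Word programs and introduction to the Internet".

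**The concern.** The paired t test is the only method on the list made for paired data. Applied to scores before and after the VR phase (T1 to T2 in G1, T0 to T1 in G2), it estimates the VR effect plus whatever eight computer classes and the passage of time do. It has no control group.

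The protocol's own rationale makes a course effect plausible. Learning the Internet is cited as tending to reduce loneliness, and the Internet is part of the syllabus. No size is given.

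The design provides a concurrent conventional group in both phases, but Section 8.3 does not say that the VR conclusion must use it. Restricting the analysis to planned comparisons gives no protection while those comparisons are unnamed. At stake is whether a reported fall in SELSA-S answers the primary question or only shows that students felt less lonely as the course went on.

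**Working it through.** **Inputs from the protocol.** Significance level 0.05 (Section 8.3; two-sided assumed). Minimum of 23 participants (Section 2.1). At most 6 × 10 = 60 students, three classes per group (Section 2.5). The figure of 23 is taken from an earlier study; no effect size, SD or power is stated, so there is no calculation to reproduce.

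**Assumptions not in the documents.** Normal scores with SD 1; within-person correlation r = 0.7; the same course-related fall c in each phase; true VR effect zero; no carryover; no clustering by class. The simulations used 6,000 runs per setting.

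**1. Paired t test before v after the VR phase, both groups pooled.** The SD of a within-person change is √(2(1 − r)) = √0.6 = 0.775. The standardised change is c/0.775, and the noncentrality is that value times √n.

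| n | c | Standardised change | Noncentrality | False-positive rate |
|---|---|---|---|---|
| 23 | 0.2 | 0.258 | 1.24 | 22% |
| 23 | 0.3 | 0.387 | 1.86 | 43% |
| 60 | 0.2 | 0.258 | 2.00 | 50% |
| 60 | 0.3 | 0.387 | 3.00 | 84% |

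Simulation with groups of 12/11 and 30/30 agrees: 22%, 43%, 51% and 84%. At c = 0 the rate is about 5%. The result depends on r: at n = 23, r = 0.5 gives 15% and 28%, and r = 0.8 gives 31% and 59%.

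**2. Paired t test of T1 v T2 in everyone,** as the one-order wording of the Abstract and Section 8 would suggest: 21% and 43% at 12/11, for c = 0.2 and 0.3.

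**3. Paired t test of each person's score after VR v after conventional classes, both sequences pooled.** The bias is (n1 − n2)/(n1 + n2) of the phase-2 fall: 1/23 = 4% at 12/11, 0% at 30/30 and 7/23 = 30% at an illustrative 15/8. For c from 0 to 0.5 the false-positive rate is 2% to 5% in the two balanced settings. At 15/8 it reaches 8.5% when c = 0.5.

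**4. Between-group tests, c from 0 to 0.5, all three group splits.**
- Mann–Whitney on T0-to-T1 change: 4.3% to 5.2%.
- Mann–Whitney on the T1 score alone: 4.0% to 4.9%.
- t test of T1-to-T2 change between sequences: 4.5% to 5.2%.

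The course effect shifts both groups equally and cancels.

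**5. Clustering.** The rates in step 4 treat persons as randomised, whereas classes are. With 10 per class and an assumed intraclass correlation of 0.02 to 0.10, the variance of the group difference is inflated by 1 + 9 × 0.02 = 1.18 to 1 + 9 × 0.10 = 1.90. The cut-off of 1.96 then acts as 1.96/√1.18 = 1.80 to 1.96/√1.90 = 1.42, which is a rejection rate of about 7% to 16% under no effect. The between-group contrast therefore keeps its 5% only if the class is allowed for.

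**The case against.** The strongest reply is that Section 8.3 does plan a G1 versus G2 comparison, that two of its listed tests are between-group tests, and that Section 1 states the VR-versus-conventional question plainly. A Mann–Whitney test at T1 or on change scores is a concurrent comparison, free of course-effect bias (step 4). A paired t test is not biased in itself either: comparing VR with conventional condition within persons is nearly free of period bias when the groups are balanced (step 3). A condensed article may also leave the mapping of tests to contrasts to a fuller plan.

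Much of this stands. A reader might infer that the plan credits the course effect to VR, or that none of its tests can answer the primary question. The documents support neither reading: no passage says VR will be judged from a within-group test, and suitable tests are on the list. A reader might also infer that the protocol expects loneliness to fall from the classes alone. The Introduction only cites background on learning the Internet, and Section 2.4 attributes the expected reduction to the games.

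What does not fall is the ambiguity. The article gives a list joined by *or*, assigns none of it, and elsewhere describes the analysis by moment alone and in a single order for everyone. A before/after test is fully compatible with that text.

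**Conclusion.** The point holds as a defect of specification. Section 8.3 allows an uncontrolled before/after paired test to be presented as the VR effect on the primary outcome; it does not require it. If that route were taken with no VR effect, the chance of a significant result would be about 22% to 43% at the minimum of 23 participants and 50% to 84% at 60, for a course effect of 0.2 to 0.3 SD per phase.

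Those sizes rest on an assumed course effect and an assumed correlation of 0.7; the protocol gives neither. With no course or time effect there is no inflation. A between-group comparison of change stays near 5% whatever the course does, provided that randomisation by class is respected.

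**What to change.** In Section 8.3:

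- State that the VR conclusion on SELSA-S rests on the G1 versus G2 difference in T0-to-T1 change, or in T1 adjusted for T0.
- For phase 2, compare the within-person T2−T1 differences between the two sequences. This removes the period effect but not carryover. The difference between sequences equals twice the VR effect if that effect has gone by the end of the next phase, and once if it fully persists, so the assumption should be stated.
- Allow for the class as the randomised unit. With six classes, a class-level comparison has 6 − 2 = 4 degrees of freedom.
- Label within-group paired t tests descriptive, with no VR conclusion drawn from them.
- Reconcile the one-order wording in the Abstract and Section 8 with the cross-over in Sections 2.5 and 2.6.

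The cost is wording and a wider interval, with no new data. Under the assumptions above with 23 people, the standard error of the pooled within-person change is √(0.6/23) = 0.16 SD. For the G1 versus G2 difference in change it is √(0.6 × (1/12 + 1/11)) = 0.32 SD, about twice as wide before any allowance for class. The narrower figure belongs to a quantity that is not the VR effect.

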### Study population

2.1

It will be a convenience sample. The participants will be students in beginning level computer classes for seniors in the CRI in Ribeirão Pires, Sao Paulo, Brazil.

Because no study was found using the short version of the Social and Emotional Loneliness Scale for Adults (SELSA-S) before and after any intervention, sample calculation was not possible. However, there will be a minimum of 23 participants in this study, based on the largest sample that used VR in older adults found in the literature.^[13]^

The CRI Ribeirão Pires offers cultural, sportive, and intellectual activities for people over 50 years old, as used in the multicenter Studies on Global Ageing and Adult Health project of the WHO.^[19]^

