### Data collection

2.6

Data collection will be in the usual computer classroom and done by the researchers and expert professionals available to help during its execution. The participants will be seated comfortably in an adjustable chair, or in their own wheelchair, whichever is the case. In order to protect confidentiality during and after the trial, the participants will be assigned numbers during data collection and their names would not be used during data analysis.

Data collection will be done at 3 times: moment 0 (T0) – before the beginning of the computer classes; moment 1 (T1) – after Phase 1; and moment 2 (T2) – after phase 2. The study flow is on Fig. 1.

In the first meeting (T0), the informed consent (IC) form will be presented and explained. After signing the IC, a characterization questionnaire, the SELSA-S,^[22]^ the Mini Mental,^[23]^ and the Brunel Mood Scale^[24]^ will be filled in, always with help of one of the researchers. Then, instructions for playing the VR games will be given verbally by the researcher. Participants will then play 3 games about which data will be collected: Random, MoviLetrando, and Reaction Time. The time for data collection will be up to 40 minutes.

During T1 and T2, the procedure will be the same as in T0, except for the IC explanation and Mini-mental testing.

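### Section 8.3 names no use of the T0 score when G1 and G2 are compared on loneliness after phase 1. Adjusting for it would cut the variance by 9% to 64% for an assumed T0–T1 correlation of 0.3 to 0.8.

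*Protocol article*

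**What the plan says.** All references are to the protocol article.

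- **Tests (section 8.3, Data analysis).** For mood and loneliness, the list is paired t tests, Kruskal–Wallis, Mann–Whitney U or Pearson correlation. The section adds: "The analysis will be blinded and will compare the 3 moments of data collection and the 2 groups (G1 and G2"). On the level it says: "The significance level will be *P* ≤ 0.05". It names no covariate-adjusted model and no test for the game measures.
- **Baseline (section 2.6, Data collection).** T0 is placed "before the beginning of the computer classes; moment 1 (T1") follows phase 1, and T2 follows phase 2. SELSA-S and the three assessment games are recorded at all three moments. Section 2.2 excludes anyone who misses one of the three assessments, so every analysed participant has a T0 value.
- **Allocation (section 2.5, Intervention).** "There are 6 groups of computer classes for beginners offered by CRI, with a maximum of 10 students each", and "the 6 classes of computer lessons for beginners will be randomly assigned into 2 groups", three classes to each. G2 has the VR games in phase 1 and G1 in phase 2. No washout is described.
- **Size (section 2.1, Study population).** The article states that "sample calculation was not possible" and that "there will be a minimum of 23 participants in this study, based on the largest sample that used VR in older adults".

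**The concern.** The main objective is to compare computer classes with VR games against conventional classes. Paired t tests within each group do not make that comparison. They show whether a group changed, not whether the two groups differ.

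Of the listed tests, that leaves Mann–Whitney and Kruskal–Wallis for G1 v G2. Applied to T1 scores, they ignore where each group began. The sample may be as small as 23 people, allocated as six whole classes, so the groups may well start at different levels of loneliness.

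The T1 comparison matters because it is the randomised contrast that carry-over from phase 1 cannot affect. Skills or social gains from the games could persist in G2 after phase 1, and section 8.3 does not name a cross-over contrast as the main analysis. At stake are the width of the interval for the T1 comparison and how far the result depends on which classes fell into which group.

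**Working it through.** **The plan's own figure.** The minimum of 23 cannot be reproduced. The article gives no effect size, SD or power, and takes the number from an earlier study.

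**Inputs from the article.** Sample size is 23 (about 11 v 12) up to 6 × 10 = 60 (30 v 30). The level is 0.05, taken as two-sided because the article does not say. There are three classes per group.

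**Assumed, not in the article.** The T0–T1 correlation r is taken as 0.3 to 0.8. An effect of 0.5 SD is used for illustration only. The intraclass correlation (ICC) within class is taken as 0 or 0.1.

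**Step 1: chance difference at T0.** Its SD, in units of the score SD, is √(1/n1 + 1/n2).

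- 11 v 12: √(1/11 + 1/12) = 0.42. The probability of a difference above 0.3 SD is 47%.
- 30 v 30: √(2/30) = 0.26. The probability is 25%.
- For whole classes of mean size m, multiply by √(1 + (m − 1) × ICC). With ICC = 0.1 and m = 23/6 = 3.83, 0.42 becomes 0.47. With m = 10, 0.26 becomes 0.36.

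**Step 2: how much reaches T1.** The expected carry-through is r times the T0 difference. A 0.3 SD imbalance gives 0.09, 0.15, 0.21 or 0.24 SD at r = 0.3, 0.5, 0.7 or 0.8.

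**Step 3: precision.** Relative to an unadjusted T1 comparison, the variance is 1 − r² with T0 as covariate and 2(1 − r) for change from T0. Power is Φ(0.5/SE − 1.96), with SE multiplied by √(1 − r²) after adjustment. Both power columns use a comparison of means, so the gain shown comes from T0 alone and not from leaving a rank test. All these figures ignore clustering by class.

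| r | variance, T0 as covariate | reduction | variance, change score | power, 23 people: unadjusted → adjusted | power, 60 people: unadjusted → adjusted |
|---|---|---|---|---|---|
| 0.3 | 0.91 | 9% | 1.40 | 22% → 24% | 49% → 53% |
| 0.5 | 0.75 | 25% | 1.00 | 22% → 28% | 49% → 61% |
| 0.7 | 0.51 | 49% | 0.60 | 22% → 39% | 49% → 77% |
| 0.8 | 0.36 | 64% | 0.40 | 22% → 52% | 49% → 90% |

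A simulation of 20,000 trials at 12 v 11 gave variance ratios of 0.79, 0.53 and 0.38 for covariate adjustment at r = 0.5, 0.7 and 0.8. These are slightly worse than the formula, as expected in a small sample.

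**Step 4: the cross-over contrast.** This is half the difference between sequences in T2 − T1. The same simulation, with equal correlation among the three moments, gave relative variances of 0.25, 0.15 and 0.10 at r = 0.5, 0.7 and 0.8. Adding T0 gave 0.26, 0.16 and 0.11, so T0 brings no precision there.

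**Step 5: cost when class is the unit.** Six classes in two groups leave 6 − 2 = 4 error degrees of freedom, and a class-mean covariate leaves 3. The critical t rises from 2.78 to 3.18. The interval narrows only if √(1 − r²) × 3.18 < 2.78, that is r² > 1 − (2.78/3.18)² = 0.24, or r above about 0.49. Here r is the correlation between class means.

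**The case against.** **The article does not rule out using T0.** The abstract speaks of evolution between the three moments, and the Discussion speaks of changes in loneliness. A Mann–Whitney test on change from T0 fits that wording and would remove additive imbalance. This stands: use of T0 is unspecified, not excluded. It does not dispose of the point. Section 8.3 names the tests and does not say they use change, and change scores gain precision only if r exceeds 0.5; below that they lose it.

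**The design is a cross-over.** Each participant receives both conditions, and stable group differences cancel in T2 − T1. This also stands. A reader might infer that imbalance at T0 remains in every estimate of the VR effect; step 4 shows that it does not. The point is confined to G1 v G2 after phase 1. On precision alone, the phase-1 comparison should not replace the cross-over contrast: at r = 0.7 the simulated relative variances are 0.53 for adjusted T1 and 0.15 for the cross-over.

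**Imbalance is not bias.** A reader might infer that the unadjusted comparison is biased or has an inflated type I error. Over repeated randomisations the unadjusted estimate is unbiased, and adjusting for T0 is not needed to hold the error rate. Any effect of class allocation on error rates is a separate matter.

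**The games.** The list in section 8.3 is introduced for mood and loneliness. For the games nothing is stated wrongly; the remedy simply extends to them.

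**Conclusion.** The point holds for the G1 v G2 comparison of SELSA-S after phase 1. As listed, the between-group tests have no place for the T0 score, which is available for everyone analysed. Using it is a better method at little cost.

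Its size depends on r, which the article does not give: a variance reduction of 9% at r = 0.3, rising to 64% at r = 0.8. A reader might infer that half or more of the precision is thrown away. That needs r of about 0.71 or higher (√0.5 = 0.71), and the documents do not support it as a general statement. The power figures further assume an effect of 0.5 SD and independent participants, so they show direction and rough scale only.

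The harm is a wider interval and a T1 result that leans on one allocation of six classes.

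**What to change.** In section 8.3, state that the G1 v G2 difference in SELSA-S at T1 is estimated from a linear or mixed model with the T0 SELSA-S score as covariate and class accounted for, and is reported as an adjusted mean difference with a 95% CI. Present it alongside the cross-over contrast that uses phase 2, not in its place. Use the same model for each game measure with its own T0 value. Do not test G1 against G2 for significance at T0.

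This takes a sentence or two. No new data are needed, and the software already planned can fit the model. The cost is one degree of freedom. That is small if participants are the unit, but not negligible if class is (4 falls to 3). In that case the gain depends on a class-level correlation above roughly 0.49, so the choice should be fixed before the data are seen.

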Considering the settings presented, we believe that motor and cognitive ability acquired through VR games might facilitate computer utilization, which is a valuable communication tool.^[17]^ Therefore, we intend to assess, through a loneliness scale, a group of older adults that are initiating computer classes for beginners. The effects of practicing games using VR within computer classes will be compared to the impact of conventional computer classes. Games with VR, requiring a variety of different motor and cognitive abilities will be used to identify whether evolution in loneliness, is related to the practice of tasks using virtual ICTs. We hypothesized that the practice of VR games added to conventional computer classes will lead to an improvement in motor ability and less loneliness of older adults.

Thus, the main objective is to evaluate the effects of practicing games in a VR environment during computer classes on loneliness among students of an elderly reference center (ERC). Moreover, in students initiating computer classes for seniors, we aim to: evaluate the evolution in time of response during the practice of VR games; evaluate the evolution in performance of practice of VR games; and evaluate the relation between motor ability to loneliness.

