## Method

2

This study protocol followed the Stardard Protocol Items for Randomized Trials (SPIRIT).^[18]^ This study will be a prospective longitudinal study with a randomized cross-over design which will use games in a VR environment within computer classes to reduce loneliness among students at an ERC.

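### Section 8.3 compares moments and sequence groups but does not designate the VR-versus-conventional contrast, a T0 adjustment, or a rank test for repeated moments

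*Protocol article*

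**What the plan says.** - **Design (section 2):** "a prospective longitudinal study with a randomized cross-over design".
- **Aim (section 1, Introduction):** "The effects of practicing games using VR within computer classes will be compared to the impact of conventional computer classes".
- **Allocation (section 2.5, Intervention):** "In phase 1, G1 will have 8 conventional computer classes, while G2 will have 8 computer classes which will include 15 minutes" of game practice. Then: "In phase 2, intervention will be crossed between the groups". Both groups therefore receive both kinds of class, in opposite order.
- **Measurement (section 2.6, Data collection):** the same people are assessed at T0 (before classes), T1 (after phase 1) and T2 (after phase 2). Section 2.2 excludes anyone who lacks one of the three.
- **Analysis (section 8.3):** the analysis "will compare the 3 moments of data collection and the 2 groups (G1 and G2". For mood and loneliness it lists paired t, Kruskal-Wallis, Mann-Whitney and Pearson correlation as alternatives and assigns none to a particular comparison. Testing is limited to comparisons planned from the hypotheses, and these are not itemised.
- **Labels elsewhere:** the Abstract (Methods and Analysis) and the opening of section 8 (Measures) place T1 after eight ordinary classes and T2 after eight classes with games, without distinguishing the groups.

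**The concern.** Because the intervention crosses over, the moment factor measures the passage of time and the group factor measures order. The VR effect appears in the difference between groups at T1, or in how that difference changes from T1 to T2. Section 8.3 names the two factors but not this contrast.

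The labels in the Abstract and section 8 make the gap more serious. A reader who takes T1 as conventional and T2 as VR for everyone would treat the pooled change from T1 to T2 as the VR effect. By section 2.5 that is correct for G1 and reversed for G2. The pooled change mixes VR with time, class attendance and retest effects.

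Two further gaps affect precision. No use of T0 is specified for the between-group comparison. The only listed rank test for more than two samples assumes independent samples, while the three moments are repeats on the same people.

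**Working it through.** **Inputs.** From the document: two sequences, three moments, significance level 0.05 (taken as two-sided), at least 23 participants (section 2.1), and at most 6 × 10 = 60 (section 2.5). The document gives no effect size, SD or within-person correlation and no power figure, so there is no stated result to reproduce. Assumed: normal scores with SD 1, equal correlation r between moments of 0.3 to 0.7, and the effects given below. Clustering by class is left out.

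**1. What each comparison estimates.** Let classes alone change loneliness by −0.3 SD per phase and let VR add −0.5 SD.

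| | T0 | T1 | T2, VR effect not retained | T2, fully retained |
|---|---|---|---|---|
| G1 (conventional, then VR) | 0 | −0.3 | −1.1 | −1.1 |
| G2 (VR, then conventional) | 0 | −0.8 | −0.6 | −1.1 |
| G2 − G1 | 0 | −0.5 | +0.5 | 0 |

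- Groups averaged over the three moments: (0 − 0.5 + 0.5)/3 = 0 if not retained, or (0 − 0.5 + 0)/3 = −0.17 if retained. The group label alone does not recover −0.5.
- Moments pooled over groups: with no VR effect at all, the means are 0, −0.3 and −0.6. The moment factor shows a fall without any VR effect.
- G2 − G1 at T1: exactly −0.5 in both cases.
- Cross-over contrast, half of (difference at T1 minus difference at T2): ½(−0.5 − 0.5) = −0.5 if not retained, but ½(−0.5 − 0) = −0.25 if fully retained. It removes the period effect but is diluted by carry-over, which is why it belongs second.

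**2. Pooled T1 versus T2, paired t test, no VR effect.** The SD of the difference is √(2(1 − r)) and the noncentrality is 0.3√n / √(2(1 − r)).

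| r | SD of difference | n=23: noncentrality, rejection | n=60: noncentrality, rejection |
|---|---|---|---|
| 0.3 | 1.183 | 1.22, 21% | 1.96, 49% |
| 0.5 | 1.000 | 1.44, 28% | 2.32, 63% |
| 0.7 | 0.775 | 1.86, 43% | 3.00, 84% |

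For T0 versus T2 the shift is 0.6 SD, and at r = 0.7 rejection is 94% (n=23) and 100% (n=60). Each of these is a true time change that would be misread if credited to VR.

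**3. Use of T0.** The residual variance of the T1 comparison is 1 for raw scores, 2(1 − r) for change scores and 1 − r² when adjusted for T0. At r = 0.3, 0.5 and 0.7, change scores give 1.40, 1.00 and 0.60; adjustment gives 0.91, 0.75 and 0.51. Adjustment has the smallest variance at each.

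**4. Kruskal-Wallis across three repeated moments.** In 4,000 simulated trials under the null at n=23, it rejected in 1.6% (r=0.3), 0.5% (r=0.5) and 0.03% (r=0.7); Friedman rejected in about 4.5%. Simulated power for a 0.4 SD shift at one moment, accurate to a few percentage points:

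| r | n=23: Kruskal-Wallis vs Friedman | n=60: Kruskal-Wallis vs Friedman |
|---|---|---|
| 0.3 | 18% vs 25% | 59% vs 62% |
| 0.5 | 14% vs 32% | 56% vs 77% |
| 0.7 | 8% vs 53% | 56% vs 94% |

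**The case against.** The strongest reply is that the document leaves the right analysis open. G1 versus G2 at T1 is the randomised VR comparison, and Mann-Whitney, which is listed, can make it. In simulation with no VR effect and r = 0.7, that test held its level at n=23 (0.052 on T1 scores, 0.047 on change from T0). The Introduction states the aim, and section 8.3 confines testing to comparisons derived from the hypotheses. This stands. A reader might infer that the listed tests can never compare VR with conventional classes; the document does not support that. The gap is that the comparison is not designated.

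A reader might also infer that T0 is ignored. It is not, since it is one of the three moments compared. Only its role in the between-group comparison is unspecified.

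Nor does the document say that Kruskal-Wallis is for the three moments. Education, marital status or the six classes could be the intended factor. The moments are the only three-level comparison section 8.3 names, so the inference is likely, but it remains an inference. The error would cost power, and at r = 0.3 the cost is small.

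Finally, section 8.2 might be read as crediting better play to VR. It says only that "Lower response time and higher performance (demonstrated by higher scores and fewer errors) will indicate an improvement in motor ability". That sets the direction of the scores, and the related aim in the Introduction is to describe evolution. Section 8.2 is not wrong in itself.

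What the reply does not answer is that section 8.3 does fix the comparisons, fixes them by period and sequence, and sits beside two passages that mislabel T1 and T2 for G2. This goes beyond detail left to a fuller plan.

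**Conclusion.** The concern holds as a failure to designate the main contrast, aggravated by contradictory labels. Section 2.5 and the descriptions in the Abstract and section 8 cannot both be true of G2. A pooled moment comparison under those labels would present time trends as a VR effect in roughly one trial in five to more than four in five, depending on n and r, if classes alone lower loneliness by 0.3 SD per phase. That class effect, the correlation and the SD are assumptions, and no passage states outright that the pooled change will be read as the VR effect. The Kruskal-Wallis point is conditional on its use across moments and concerns lost power only. The reasoning about what moment and group estimate needs no assumption beyond the design.

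**What to change.** 1. In section 8.3, name G2 − G1 at T1, adjusted for the T0 score, as the VR effect on SELSA-S.
2. Name the period-adjusted cross-over contrast (group-by-moment over T1 and T2) as secondary. Take both from one baseline-adjusted model with a random participant effect that allows for class.
3. Use Friedman for any rank test across the three moments.
4. Correct the Abstract and the opening of section 8 so that T1 and T2 are described by phase, in agreement with section 2.5.
5. Apply the same between-group contrast to the game outcomes. The same three games are replayed at every assessment, so improvement over time cannot by itself show a VR effect.

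The cost is analysis wording and slightly more analysis work; the model can be fitted with SPSS MIXED and no new data are needed. With six classes, three per group, class-level variance will be poorly estimated, and the report should say so.
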